### Example

Weight = 30 kg. P-Na^+ ^at T_0 _= 140 mmol/L.

24 h infused volume according to study protocol (Table 1) = 1410 ml.

24 h insensible (~45 ml/100 cal per 24 h) = 765 ml [22].

The expected 24 h urine output needed to maintain water balance will be as follows: infused volume - insensible losses = 645 ml.

By infusing 0.23% salt solution (40 mmol/L Na^+ ^+ 20 mmol/L K^+ ^+ 60 mmol/L Cl^-^) in 5% glucose, the electrolyte intake (and therefore excretion) will be expected to be as follows:

At a fixed urine osmolality of 900 mosmol/kg H_2_O, because of hypothetically persistent ADH release, our example case will be expected to produce 188 ml urine per 24 h (i.e., solute load of 169.2 mosmol ÷ urine osmolality of 900 mosmol/kg H_2_O) [22]. As a consequence, 457 ml of water will be retained (645 ml - 188 ml); ⅔ of this will distribute to the intracellular fluid compartment and ⅓ to the extracellular fluid compartment [41]. Since the apparent volume of distribution of sodium is the total body water (TBW) [42], and the estimated TBW accounts for 60% of body weight [43], the expected change in p-Na^+ ^can be treated algebraically as follows:

where the subscripts _i _and _f _represent initial and final states, respectively. This equation states that the initial volume × initial concentration = final volume × final concentration. Since we assume that in our hypothetical case there will be no change in total body sodium content by the end of the first postoperative 24 h, the p-Na^+^_f _is now the original sodium content divided by TWB_f_. Thus, in our example the p-Na^+^_f _will be expected to be 136.5 mmol/L (i.e., p-Na^+^_f _= 18 L × 140 mmol/L ÷ 18.457 L).

If we replace 0.23% sodium chloride parenteral fluid therapy with either 0.40% sodium chloride or 0.81% sodium chloride, the expected p-Na^+^_f _would be 136.4 mmol/L and 138.2 mmol/L, respectively.

#### Sample size calculation

The expected sample size required in our study is based on the calculation for equality applied to the primary outcome variable p-Na^+^, measured at T_24 _as mmol/L.

In the previous section we estimated that the largest expected fall in p-Na^+ ^in our illustrative case would be 3.6 mmol/L. Consequently, if we apply this figure to a patient whose p-Na^+ ^at T_0 _is 135 mmol/L, the expected p-Na^+ ^at T_24 _after giving 0.4% sodium chloride would be 131.4 mmol/L, a plasma level which may not have clinical significance [27]. However, we are compelled to speculate that this figure may not be exact because in our illustrative case we dealt with hypothetical data that may not necessary mirror the clinical setting. Hence, our estimate has to be verified by means of water and electrolyte balance measurement *in vivo*. Taken this uncertainty into account, we arbitrarily decided that the equality margin will be set at 5 mmol/L. This value will capture our estimate, but, most importantly, in patients whose p-Na^+ ^at T_0 _is 135 mmol/L, it would allow us to identify those patients who are at risk for developing hyponatremia of potential clinical significance [27]. Thus, a difference between treatment groups greater than this margin will be considered as clinically relevant. Consequently, a difference smaller than 5 mmol/L will be considered as clinically less relevant. Sample size was calculated assuming a standard deviation (SD) of 5 mmol/L, a significance level of 0.05, and a power of 80% to detect a difference larger than the equality margin of 5 mmol/L. Hence, the number of patients per study arm needed to fulfill the power goal of the study will be 17 patients.

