**Methods/Design:**

Our prospective randomized non-blinded study will be conducted in healthy children and adolescents aged 1 to 14 years who have been operated for acute appendicitis. Patients will be randomized either to intravenous hypotonic (0.23% or 0.40% sodium chloride in glucose, respectively) or near-isotonic (0.81% sodium chloride in glucose) solution given at approximately three-fourths of the average maintenance rate. The main outcome of interest from this study is to evaluate 24 h post-operatively whether differences in p-Na^+ ^between treatment groups are large enough to be of clinical relevance. In addition, water and electrolyte balance as well as regulatory hormones will be measured.

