## Methods

### Objectives

Our primary outcome of interest is to evaluate whether the post-operative prescription of either hypotonic or near-isotonic fluid therapy given at low maintenance rate in otherwise healthy children with normal post-operative p-Na^+ ^are equally effective in maintaining p-Na^+ ^within the normal range. In addition, our secondary aim is to determine water and electrolyte-balance following the administration of the investigational parenteral maintenance fluids as well as to investigate known regulatory hormones involved in the homeostatic control of water balance. Finally, we will seek to determine how frequently p-Na^+ ^should be monitored during the post-operative period.

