#### Data analysis

All statistical analyses will be described in detail in the statistical analysis plan. Data will be presented using descriptive statistics, i.e., mean and SD for continuous variables, and frequency and proportions for categorical variables. The efficacy variable will be evaluated using ANCOVA, intervention (parenteral maintenance fluid therapy) as a fixed factor and baseline levels as a covariate in the model. The corresponding 95% confidence intervals for each group and the difference between groups will also be presented. In addition, graphs will be used in order to facilitate the interpretation of the results regarding the equality margins to be used in the present study.

Missing data will be replaced using a conservative approach, which will be specified in the statistical analysis plan. All tests will be two-sided and performed at the significance level of 0.05.

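### The 80% power applies to rejecting zero difference when the truth is 5 mmol/L, not to showing a difference above 5 or to concluding that the fluids are alike within 5

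*Protocol article*

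**What the plan says.** The protocol article frames the primary question in two ways. Under Objectives, it is whether the hypotonic and near-isotonic fluids "are equally effective in maintaining" plasma sodium in the normal range. In the abstract (Methods/Design), it is whether the differences "between treatment groups are large enough to be of clinical relevance".

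Under Sample size calculation, the required size "is based on the calculation for equality applied to the primary outcome variable", plasma sodium at 24 h. The margin is then fixed: "we arbitrarily decided that the equality margin will be set at 5 mmol/L". A between-group difference above it counts as clinically relevant, while "a difference smaller than 5 mmol/L will be considered as clinically less relevant". The inputs are stated as "assuming a standard deviation (SD) of 5 mmol/L, a significance level of 0.05", with "a power of 80% to detect a difference larger than the equality margin of 5 mmol/L", giving 17 per arm.

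Under Data analysis, the efficacy variable is analysed by ANCOVA with baseline as covariate. Confidence intervals at 95% are planned for each group and for the between-group difference, and graphs will help to read the results against the margin. "All tests will be two-sided and performed at the significance level of 0.05". Further detail is left to a statistical analysis plan that is not shown.

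**The concern.** A margin within which treatments count as alike belongs to an equivalence question. A sample size that gives power to detect a difference belongs to the opposite question. The article uses both and attaches one power figure, so a reader may take the 80% as the chance of a sound answer to the question in the Objectives.

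The power sentence is also inaccurate as a statement about differences. A test of zero difference that has 80% power at a true difference of 5 does not have 80% power to show that the difference exceeds 5.

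The reading rule compares a difference with 5 and does not say that the confidence interval must lie inside the margin. The article ties the margin to children who start at 135 mmol/L and could reach the 130 mmol/L region, so a mistaken finding of likeness would bear on safety.

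**Working it through.** **Inputs.** Margin 5, SD 5, two-sided alpha 0.05, power 80% and 17 per arm (Sample size calculation); three arms (Study Design); predicted 24 h sodium of 136.5, 136.4 and 138.2 mmol/L (Example). The largest predicted gap is 138.2 − 136.4 = 1.8.

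**1. The plan's own figure.** For a two-sample t-test, the standard error of a difference is SD × √(2/n) and the noncentrality is 5 divided by that standard error.
- n = 16: SE = 5 × √(2/16) = 1.768, noncentrality 2.83, 30 df, power 78.1%.
- n = 17: SE = 5 × √(2/17) = 1.715, noncentrality 2.92, 32 df, power 80.7%.

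So 17 is the smallest number that reaches 80%. The arithmetic is right, and the hypothesis it serves is rejection of zero difference at a true difference of 5.

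**2. Showing a difference above 5.** If the true difference is exactly 5, a 95% CI lies wholly above 5 in 2.5% of trials, by construction. With the variance pooled over three arms (48 df), the half-width is 2.011 × 1.715 = 3.45, so the observed difference would have to exceed about 5 + 3.45 = 8.45. Even at a true difference of 8 this happens about 40% of the time.

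**3. Concluding likeness within 5.** The criterion is that the observed difference plus or minus the half-width stays inside (−5, +5). The half-width is 3.45 for a 95% CI and 1.677 × 1.715 = 2.88 for a 90% CI. Power per pair, 17 per arm, SD 5, 48 df, integrating over the sampling distribution of the variance:

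| True difference | 95% CI | 90% CI |
|---|---|---|
| 0 | 63.0% | 78.1% |
| 1.8 | 42.1% | 56.5% |

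With two-arm degrees of freedom (32), the figures are 61% and 77% at zero, and 41% and 56% at 1.8. On that two-arm basis, 80% equivalence power needs 23 (95% CI) or 18 (90% CI) per arm at zero true difference, and 40 or 31 at 1.8.

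**4. The reading rule.** If it is applied to the point estimate and the true difference is 5, the estimate is centred on 5 and its absolute value falls below 5 with probability 0.50. An observed 4.9 would be labelled less relevant, although its 95% CI would reach about 4.9 + 3.45 = 8.35.

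**5. Sensitivity to baseline adjustment.** The article gives no residual SD after ANCOVA. Assuming 4.5, power per pair is about 78% (95% CI) or 88% (90% CI) at zero, and 52% or 65% at 1.8.

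**The case against.** The strongest reply is that this is a difference trial with loose wording. The Objectives ask whether the fluids are equally effective and do not undertake to show it. The abstract poses a difference question, and the sample size section openly calls its method a calculation for equality, a usual label for testing equal means. On that view 17 per arm fits. This stands in part: the objective is ambiguous, and a reader who infers a declared equivalence trial with the wrong test goes beyond the text. It does not rescue the power sentence, which still claims a difference larger than the margin. A positive answer to the Objectives would also still have no rule or power behind it.

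A second reply is that the analysis plan may hold the decision rule, and that the planned CIs and graphs are the right tools for one. That is fair as far as the detail goes. But the margin, its reading and the 80% are fixed in this article, and no later plan can make the 80% apply to another hypothesis.

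A third reply is that the shortfall is small under the usual equivalence convention: 78% against 80% with a 90% CI and no true difference, where 18 per arm would do. That is correct. The gap is material with the 95% CI that the article plans, or at its own predicted difference.

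Two further inferences are unsupported. Nowhere does the article say that a non-significant test will be taken as equality. Nor does it require all three pairs to be alike together, so joint power over the pairs is not the relevant figure.

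**Conclusion.** The point holds as a mismatch between the stated power and the conclusions that the article describes. The 17 per arm is correctly computed for rejecting zero difference at a true difference of 5. It gives neither 80% power to show a difference above 5 nor 80% power to conclude likeness within 5. The latter is about 63% or 78% per pair at zero true difference, and about 42% or 56.5% at 1.8, for a 95% or 90% CI respectively.

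These figures assume normal data, SD 5, no dropout and no gain from the baseline covariate. They rise if the residual SD is smaller. The 50% mislabelling figure holds only if the reading rule is applied to the point estimate, which the article neither says nor excludes.

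It might seem to follow that a relevant difference should be declared only when the CI lies wholly beyond 5. The article does not ask for this, and at this sample size such a rule would almost never succeed at a true difference of 5.

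**What to change.** Keep 17 per arm and make three changes before enrolment, which the article says will start only after publication.

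1. Restate the power: 80% power to reject no difference when the true difference is 5 mmol/L (SD 5, two-sided 0.05).
2. State how the margin is read. Two fluids are called equally effective only if the CI of the ANCOVA-adjusted difference, at a confidence level fixed in advance, lies wholly within (−5, +5). A CI that excludes zero shows a difference, and its clinical relevance is read from where the CI lies against the margin. Any other result is inconclusive, and non-significance alone is not evidence of equality.
3. Report the equivalence power at 17 per arm and SD 5, per pair: about 63% (95% CI) or 78% (90% CI) at zero true difference, and about 42% or 56.5% at the predicted 1.8. Add that baseline adjustment may raise these, with any assumed residual SD stated.

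The cost is wording in the protocol and analysis plan, with no extra patients, since the adjusted analysis and CIs are already planned. The downside is that the stated power for the equality conclusion becomes less favourable.

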#### Data analysis

All statistical analyses will be described in detail in the statistical analysis plan. Data will be presented using descriptive statistics, i.e., mean and SD for continuous variables, and frequency and proportions for categorical variables. The efficacy variable will be evaluated using ANCOVA, intervention (parenteral maintenance fluid therapy) as a fixed factor and baseline levels as a covariate in the model. The corresponding 95% confidence intervals for each group and the difference between groups will also be presented. In addition, graphs will be used in order to facilitate the interpretation of the results regarding the equality margins to be used in the present study.

Missing data will be replaced using a conservative approach, which will be specified in the statistical analysis plan. All tests will be two-sided and performed at the significance level of 0.05.

## Discussion

Post-operative symptomatic hyponatremia in patients receiving intravenous maintenance fluid therapy may be associated with severe cerebral dysfunction and high mortality [44]. Our study intends therefore to address a question that might have important clinical implications. To put our study question into perspective, we summarize the results of the most relevant pediatric studies published so far on this topic.

A retrospective single-center study reported on the incidence and clinical consequences of post-operative hyponatremia in children [45]. Out of 145 pediatric patients who met the criteria for further analysis, 16 children were identified as having had p-Na^+ ^< 130 mmol/L during the 24 h following the surgical procedure. In the post-operative period, the incidence of hyponatremia was similar between patients receiving hypotonic and isotonic fluid therapy. None of them experienced neurological sequelae due to hyponatremia. According to the data presented in this study, and by excluding one patient because of pseudohyponatremia, it seems that in 14 of the 15 patients the rate of infusion of parenteral fluid therapy given over the 24 h following the surgical procedure was almost equal (*n *= 8), equivalent (*n *= 4), or higher (*n *= 2) than the average maintenance fluid therapy that would otherwise be recommended to healthy children under normal clinical conditions [22]. This observation suggests that the volume and not the composition of intravenous solutions used for parenteral fluid therapy might have accounted for the development of post-operative hyponatremia.

One study, including medical and surgical patients followed from 12 to 24 h after admission, found that the prescription of 0.18% sodium chloride in 5% glucose (30 mmol/L Na^+^) was associated with a significant fall in p-Na^+ ^when compared with patients who received isotonic saline (0.9% sodium chloride, 154 mmol/L Na^+^) [6]. The incidence of hyponatremia was not reported. Full maintenance parenteral fluid therapy was found to produce a greater but not significant fall in p-Na^+ ^than the fluid therapy administered at a restricted rate.

A separate investigation, also designed as a randomized controlled study, conducted in critically ill medical and surgical patients, showed that at 24 h of starting full maintenance parenteral fluid therapy the fall in p-Na^+^, often to mild hyponatremic levels, was higher in patients receiving fluids with a sodium content < 100 mmol/L compared with patients receiving intravenous solutions containing 140 mmol/L Na^+ ^[7].

Although the aforementioned investigations were designed to provide the most reliable form of scientific evidence, they have some limitations that weaken the power of the studies, e.g., study population heterogeneity, wide age-range groups, no water and electrolyte balance, no measurement of regulatory hormones, no standardization of fluid therapy given intra-operatively, and short follow-up. Still, these investigations are important since they indicate that a hospital-acquired decrease of p-Na^+ ^in patients receiving parenteral maintenance fluid therapy may be avoidable.

A recent randomized trial comparing multiple post-operative intravenous maintenance fluid treatment groups determined the risk of hyponatremia in patients aged between 6 months and 15 years admitted for either elective or emergency surgery [46]. The authors observed that 24 h after surgery, regardless of fluid rate, i.e., either 100% or 50% maintenance fluid rate, there was no difference in the incidence of hyponatremia between patients who received 0.9% sodium chloride and 0.45% sodium chloride. On multiple linear regression analysis, hypotonic fluid, but not rate, significantly influenced the change in p-Na^+ ^from induction of anesthesia to 24 h after surgery. It is important to observe, that at this time-point after surgery, no patient in either treatment arm group experienced a fall in p-Na^+ ^below 130 mmol/L. This study did not report on both the total intravenous volume prescribed after surgery and urinary production, making therefore difficult to analyze the role of water and electrolyte balance on p-Na^+ ^values at 24 h after surgery.

Finally, in a previous prospective study investigating the incidence of post-operative hyponatremia in pediatric patients who uniformly received hypotonic parenteral fluid therapy at full maintenance rate [47], the prevalence of hyponatremia, defined as p-Na^+ ^< 136 mmol/L, was 21% and 31% at 12 h and at 24 h following surgery, respectively. Of note, no patient experienced a decrease in p-Na^+ ^below 130 mmol/L, suggesting that the inclusion of an hypotonic saline administration arm in future clinical trials is a feasible option [48].

In the present paper we describe the objectives of our study and the design to achieve them. Since no consensus has been reached on post-operative fluid management, the results of this investigation will contribute to the evidence base for effective pediatric prescription of parenteral maintenance fluid therapy in otherwise healthy children and adolescents undergoing acute surgery. Although our investigation will be conducted in a homogeneous cohort of patients, we speculate that our results would be of clinical importance, not only in post- appendectomized children and adolescents but also in other post-operative scenarios.
